**Fig. 3 Fig3:**
[figure not shown]
The intervention will be performed with medical device of invasive laser acupuncture needle, low-level laser, and electrical stimulator (Ellise)

All participants should comply with the protocol procedures such as the allocated intervention and treatment schedules. However, the treatment schedule may be changed according to the judgment of the PI or the request of the participant.

During the clinical trial period, all participants will be allowed to continue the routine management regimens, existing medications (e.g., those for hypertension, diabetes, or hyperlipidemia), and medications for maintaining and improving their health status. However, they will not be permitted to engage in other treatments (pharmacological treatments, physical therapy, or CAM therapies) to ameliorate their CLBP symptoms. All medical devices will be inspected by the investigators, who will record the results of checkups in the management register.

### Outcome measurements

In accordance with the study objective, improvements in pain intensity assessed using the VAS will be considered the primary outcome, and the secondary outcomes will be the changes in ODI and EQ-5D-5L. VAS, ODI, and EQ-5D-5L scores will be recorded before intervention, at the end of intervention, and 4 weeks after the completion of the intervention. The primary end point will be the VAS score recorded at the end of the intervention.

The VAS is a 10-cm-long straight line marked at each end with the anchor labels “no pain” and “pain as bad as it could be” [28]. Participants will be asked to mark a point representing the severity of their pain. Scores are recorded in millimeters, and the total score ranges from 0 to 100 mm [29].

The ODI has become one of the principal condition-specific outcome measures used in the management of spinal disorders [30]. The validated Korean version of the ODI, which excludes sexual life items from the original ODI, contains 9 questions about daily activities, including inventories of pain intensity, personal care, lifting, walking, sitting, standing, sleeping, social life, and traveling. Each question is rated on a scale from 0 to 5 points, with higher scores indicating greater severe pain-related disability [31].

The validated Korean version of the EQ-5D includes generic questions about personal health-related quality of life and 5 dimensions pertaining to mobility, self-care, usual activities, pain/discomfort, and anxiety/depression. Each dimension has 3 response categories, namely “none,” “some,” and “extreme/unable to,” with lower scores indicating a better state of health [32, 33]. The EQ-5D-5L is a new version of the EQ-5D that includes 5 levels of severity (none, slight, moderate, severe, and extreme/unable) for each of the 5 EQ-5D dimensions [34].

### Incidence of AEs

AEs are undesirable and unintentional signs, symptoms, or diseases that appear during or after treatment in a clinical trial. Participants in this study will be required to voluntarily report any AEs. All AEs that occur during the trial will be documented. AEs that could occur in this study include skin irritation, bleeding, local hematoma, pallor, sweating or dizziness, fainting during acupuncture treatment, continuous severe pain for > 1 h after acupuncture treatment, objective worsening of existing symptoms, and undesirable and unintentional signs, symptoms, or diseases. The CRC will record all AEs in detail, including the time and date of occurrence, degree of severity, any measures related to the treatment of the AE, and any potential causal relationships between the treatment and the AE. All AEs will also be reported to the PI and relevant IRB. In case of SAEs, defined as AEs causing severe disability or malfunction, appropriate measures will be taken, and the incident will be immediately reported to the PI and relevant IRB. In cases in which an AE occurs because of the clinical trial, participants will notify the CRC and PI and will be compensated.

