### Randomization

After the acquisition of written informed consent, the practitioners who will be performing the intervention will conduct a screening interview. Then, the assessor will perform baseline measurements for participants who meet the inclusion criteria. The 45 enrolled participants will be immediately assigned serial numbers generated using the SPSS version 21 software (IBM Corp., Armonk, NY, USA) and randomly allocated to 1 of the 3 study groups (*n* = 15 per group). The serial number codes will be inserted in opaque envelopes that will be sealed and stored in a double-locked cabinet; these will be opened by the PI or practitioners who will perform the intervention in the presence of the patient and a guardian.

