### Implementation

The CRC will generate the allocation sequence, enroll participants, and assign participants to the interventions.

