## Discussion

Although LA has long been used in the treatment of CLBP, the efficacy and optimal treatment method of LLLT (including LA) for CLBP remains controversial owing to insufficient evidence. We designed this study to investigate the efficacy of ILA and the effects of different wavelengths of ILA on CLBP. The design of this study, including the treatment method, schedules, and outcome measurements, is based on the design of several studies that evaluated various types of acupuncture treatment for LBP [10, 13, 14, 19, 24, 25, 27]. The two modalities of ILA (650 and 830 nm) are based on our previous studies that showed that ILA has significant effects on neuropathic pain [37] and osteoarthritis [38] in rat models and previous RCTs that investigated the efficacy of LLLT on CLBP [13, 14].

Changes in VAS pain score will be recorded as the primary outcome, while changes in ODI and EQ-5D-5L scores will be recorded as secondary outcomes. This study will evaluate the effects of different wavelengths of ILA on pain reduction, pain-related functional disability, and quality of life in patients with CLBP.

This protocol has some limitations. First, owing to the lack of adequate preliminary studies and limited funding, this survey was designed as a single-center pilot study with a small sample size. Second, while previous LA studies on CLBP used noninvasive LA [13, 14, 19], we will only use ILA. Third, the factors that affect the effects of LA are wavelength, energy dose, and selected acupoints; however, we will only investigate the effects of wavelength. Fourth, although participants will be blinded to the group allocation and all outcome measures will be measured and recorded by an independent researcher to minimize the risk of detection bias, the acupuncturists cannot be blinded to the group allocation owing to the nature of LA.

Nevertheless, the results of this study are expected to provide preliminary evidence regarding the usefulness, safety, and efficacy of ILA for the treatment of CLBP and the effects of different wavelengths of ILA, and thus will provide a foundation for further research.

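### Adverse events are recorded by the coordinator who generates and assigns the allocation, and nobody named in the trial's own adverse-event chain is assured to be blind

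*Protocol article*

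**What the plan says.** The section Incidence of AEs sets out the chain. It starts with the participant: "Participants in this study will be required to voluntarily report any AEs". The coordinator then documents the event: "The CRC will record all AEs in detail, including the time and date of occurrence, degree of severity". The list of items goes on to measures taken and "any potential causal relationships between the treatment and the AE". After that, "All AEs will also be reported to the PI and relevant IRB". An SAE is defined there by the event causing severe disability or malfunction.

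The section Implementation gives the same coordinator a second role: "The CRC will generate the allocation sequence, enroll participants, and assign participants to the interventions". The section Randomization says of the allocation envelopes that "these will be opened by the PI or practitioners who will perform the intervention in the presence of the patient and a guardian".

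The separate assessor appears in Randomization and Blinding, for baseline and outcome assessments only. The Discussion says that "all outcome measures will be measured and recorded by an independent researcher to minimize the risk of detection bias". Outcome measurements lists those measures as the VAS, ODI and EQ-5D-5L; AEs are not among them.

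Under Statistical analysis, AE and SAE incidence is summarised by group and tested with a chi-square or Fisher exact test. Confidentiality and data management describes the CRC as standing outside the data collection phase.

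**The concern.** Safety is a stated purpose of the trial (Abstract, Background, Sample size estimation). The article accepts that 45 participants cannot settle efficacy, so descriptive safety data are among the more useful things that this pilot can deliver.

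The person who writes down each event, its severity and its relation to treatment is also the person who generated the sequence and assigned the arm. The next recipient inside the trial, the PI, may have opened the envelope. The article discloses that the acupuncturists cannot be blinded. It does not disclose that AE recording may be unblinded too.

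Some AE decisions need judgement: whether a complaint is an objective worsening of an existing symptom, whether it falls under the open-ended last category, and whether a disability is severe enough to make the event serious. If the recorder knows whether the laser was off, on at 650 nm or on at 830 nm, those decisions can differ by arm with no true difference in safety.

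**Working it through.** **Roles, side by side**

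| Step | Who | Assured blind to the arm? |
|---|---|---|
| Reports the event | Participant | Yes, by design (Blinding; Interventions) |
| Documents the event, severity and causal relation | CRC | No: generates the sequence and assigns (Implementation) |
| Receives the report inside the trial | PI | No: may open envelopes (Randomization) |
| Receives the report outside the trial | IRB | Not stated; no classifying role described |
| Measures VAS, ODI, EQ-5D-5L | Assessor | Described as separate and independent, not expressly as blinded; no AE task |

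Randomization and Implementation differ on who reveals the assignment. On either reading, a coordinator who generated the list and assigns participants can know the arm.

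**Where judgement can reach the planned test.** The test is on incidence. Relatedness does not enter it. Severity enters only through SAE status. The routes are therefore (a) which reports are documented as AEs, and (b) which AEs are classed as SAEs. Severity and relatedness matter for descriptive reporting.

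**Size.** The arm size reproduces: 12 / (1 − 0.20) = 15 per arm, and 3 × 15 = 45. One participant reclassified moves an arm by 1/15 = 6.7 percentage points, and two by 13.3.

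The article gives no AE rates, so the following are assumptions. Let π be the true proportion with an AE in both of two arms, and m the share of those participants who go undocumented in one arm only. The false gap is π × m, or 15 × π × m participants. The last column is the chance of p < 0.05 from an exact two-sided Fisher test, 15 v 15.

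| π | m | Gap (points) | Participants of 15 | Chance of p < 0.05 |
|---|---|---|---|---|
| 20% | 25% | 5 | 0.75 | 2.1% |
| 20% | 50% | 10 | 1.5 | 4.1% |
| 30% | 25% | 7.5 | 1.125 | 2.9% |
| 30% | 50% | 15 | 2.25 | 7.8% |
| 40% | 25% | 10 | 1.5 | 3.4% |
| 40% | 50% | 20 | 3 | 11.2% |

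With m = 0 the chance is 1.6% to 1.7%. The test is weak at this size: starting from no events in one arm, it takes 0 v 5 to reach p < 0.05 (p = 0.042).

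The bias can also hide a difference. With true rates of 20% v 50%, the chance of detection is 24.6%. If 25% of those affected in the higher arm go undocumented, the recorded rate there is 0.50 × 0.75 = 37.5% and the chance falls to 8.8%. If 50% go undocumented, the recorded rate is 25% and the chance is 2.3%.

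**The case against.** The strongest defence is that the compared count starts from blinded participants who report their own events, under a rule that all AEs are documented. Several listed events are observable signs (bleeding, hematoma, pallor, sweating, fainting), the pain item has a one-hour limit, worsening has to be objective, and the SAE threshold is high. The text also says that the CRC records severity and causality, not that the CRC decides them. The article condenses a fuller protocol and refers to operating procedures and report forms that are not shown.

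Much of this stands. Blinded reporting and the document-all rule make large distortions of incidence less likely, and the higher values of m above should be read in that light. They protect the report, however, and not the decision whether it counts as an AE or is serious. On recording versus grading, the only other trial recipient named is the PI, who may also know the arm, so blinded judgement is assured on neither reading. The finding rests on roles that the article assigns, not on a detail that it leaves out.

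A reader might also infer that the Discussion contradicts the AE section, because it promises independent recording of all outcome measures. The documents do not support that: AEs are not among the listed outcomes, so they fall outside the promise without contradicting it. The conflict that does exist is with Confidentiality and data management, which places the CRC outside data collection although the AE section has the CRC collecting AE data.

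**Conclusion.** The concern holds in a limited form. The article sets up an AE chain in which no trial staff member is assured to be blind, and it plans a between-group comparison of what that chain produces. The bias can act on which reports become AEs, which AEs become SAEs, and any descriptive account of severity or relatedness.

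Under assumed true rates of 20% to 40% and 25% to 50% of affected participants undocumented in one arm, the false gap is 5 to 20 points. These rates are illustrative, and the documents do not show that such under-recording occurs. With 15 per arm the main harm is to the descriptive safety evidence rather than to a p value.

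Two stronger readings are not supported. A reader might infer that biased attribution of events to treatment would distort the planned test, but that test uses incidence and relatedness does not enter it. A reader might also infer that every comparison turns on knowing whether the laser was on. That fits sham against either real arm; the 650 nm and 830 nm arms differ in wavelength.

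**What to change.** 1. State that the existing separate assessor has no access to the allocation, and have the assessor ask one fixed AE question at the week 4 and week 8 assessments.
2. Have the CRC log events between those visits as factual descriptions: what happened, when, how long it lasted and what was done.
3. For the group summary, have AE and SAE classification, severity and causality assigned from those descriptions with the arm masked, by the assessor or another already named researcher without allocation access. The researcher on the data monitoring committee who is outside data collection is a candidate only if kept from the allocation, since the PI and CRC sit on the same committee.
4. Leave immediate handling and SAE reporting as they are.
5. Reconcile Implementation, Incidence of AEs, and Confidentiality and data management on whether the CRC collects data.

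The cost is one question at two existing visits, changes to protocol and form wording, and slightly later final classification. No new staff are needed. Quality assurance requires revisions to be approved by the Ministry of Food and Drug Safety and the IRB. Trial status says that recruitment has closed and procedures were expected to finish by the end of December 2020, so the visit question may come too late. Masked classification from the recorded descriptions is still possible before analysis, and unblinded recording should then be reported as a limitation.

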### Blinding

Owing to the nature of LA treatment, a double-blind study design cannot be adopted. Therefore, we will adopt a patient-blinded trial procedure using sham LA. During the course of this clinical trial, the assessor will have no contact with the participants other than at the time of assessment. Furthermore, unblinding will not be permitted under any circumstances. However, if an SAE occurs, unblinding will be permitted after an agreement between all the researchers involved. To prevent selection, performance, and attrition biases due to the unblinded participants and practitioners, this study will only involve individuals without conflicts of interest or preconceived positions. All the practitioners who will perform the interventions will receive training in clinical trials before participation. A statistician not involved in the design or execution of the clinical trial will analyze the final data.

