### Statistical analysis

A statistician not involved in data collection will analyze the final data. We will perform a full analysis set (FA group) to assess the efficacy and a supplementary per-protocol analysis (PP group). We will compare the results of the statistical analyses between the FA and PP groups and confirm any statistically significant differences between the groups. If a significant difference exists between the PP and FA groups, the cause will be reviewed and reflected in the efficacy assessment. Missing values will be obtained using the “last observation carried forward” method. Interim analyses will not be performed. All statistical analyses will be performed using the SPSS version 21 software.

Baseline characteristics will be described and compared between the groups. Continuous data will be presented as means and standard deviations and compared using the independent *t* test or Mann-Whitney *U* test (nonparametric test). Categorical data will be presented as frequencies and percentages and compared using the chi-square or Fisher exact test.

Within each group, changes in VAS, ODI, and EQ-5D-5L scores at 4 weeks (the end of intervention) and 8 weeks (4 weeks after the end of intervention) after the start of intervention, relative to the baseline score, will be analyzed using a paired *t* test or Wilcoxon signed rank test (nonparametric test). Trends over time and time-by-treatment interactions will be explored using repeated-measure analysis of variance. The degrees of changes in the VAS, ODI, and EQ-5D-5L scores at each time point between the groups will be evaluated using the independent *t* test or Mann-Whitney *U* test (nonparametric test). Subanalyses will be performed according to participant age. All reported *p* values will be two-sided, with 95% confidence intervals. A *p* value < 0.05 will be considered statistically significant.

A safety assessment will be performed for all AEs that will occur during the study period. The incidence of AEs and SAEs will be summarized by group and analyzed using the chi-square or Fisher exact test.

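### The SAE definition covers only severe disability or malfunction, so a death, life-threatening event or admission without it would be reported as an AE but miss the SAE rules and the SAE count

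*Protocol article*

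**What the plan says.** Incidence of AEs defines seriousness in one clause: "In case of SAEs, defined as AEs causing severe disability or malfunction". For such an event, "the incident will be immediately reported to the PI and relevant IRB". For every AE the section says "All AEs will also be reported to the PI and relevant IRB", with no time limit. It also says "All AEs that occur during the trial will be documented" and gives the recording to the coordinator: "The CRC will record all AEs in detail, including the time and date of occurrence, degree of severity". On how AEs come to light it says "Participants in this study will be required to voluntarily report any AEs".

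Three other sections use the SAE term without redefining it:

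- Dropout criteria, item 2, lists an SAE as a ground for leaving the trial.
- Blinding rules out unblinding altogether and then makes one exception: "if an SAE occurs, unblinding will be permitted after an agreement between all the researchers involved".
- Statistical analysis: "The incidence of AEs and SAEs will be summarized by group and analyzed using the chi-square or Fisher exact test".

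**The concern.** An SAE definition picks out the events that need urgent handling and separate counting. This one rests on a single kind of consequence. An admission for bleeding or infection after needling that resolves fully leaves no severe disability, and on the printed wording it is not serious. The same holds for a life-threatening episode with full recovery, and literally for a death.

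The intervention is an invasive device, and the article names safety among the things the pilot is to inform. If the definition is applied literally, the most important events could be reported without urgency and be absent from the SAE line of the results. A later trial would then build on an SAE count that does not mean what its readers expect.

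**Working it through.** **1. Tracing the definition.** The main point is a matter of reading. Take an event that is fatal, life-threatening or leads to admission, but does not meet the disability or malfunction criterion:

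| Rule | Section | Does it apply as written? |
|---|---|---|
| Documented and recorded by the coordinator | Incidence of AEs | Yes, as an AE |
| Reported to the investigator and IRB | Incidence of AEs | Yes, no time limit |
| Reported immediately | Incidence of AEs | No |
| SAE dropout criterion (item 2) | Dropout criteria | No |
| Exception to the unblinding ban | Blinding | No |
| Counted in AE incidence | Statistical analysis | Yes |
| Counted in SAE incidence | Statistical analysis | No |

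The event stays visible as an AE but misses four rules tied to the SAE label. For a death the dropout item has no practical effect; the other three still matter.

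**2. The plan's own figure.** Sample size estimation takes 12 per arm and 20% dropout: 12 / (1 − 0.20) = 15 per arm, and 3 × 15 = 45. This reproduces. It supplies the denominators below and has no bearing on the definition.

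**3. What zero events would exclude (secondary).** With no events in n, the exact two-sided 95% upper limit is 1 − 0.025^(1/n).

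- One arm, n = 15: 1 − 0.025^(1/15) = 21.8%.
- Both laser arms, n = 30: 1 − 0.025^(1/30) = 11.6%.

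A pairwise two-sided Fisher test is similarly weak. For 0/15 against 4/15, p = 2 × C(15,4)/C(30,4) = 2 × 1365/27405 = 0.0996. For 0/15 against 5/15, p = 2 × 3003/142506 = 0.042. These figures describe the sample size under any SAE definition; they do not measure the defect in step 1.

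**4. Under-capture (illustration only).** The article gives neither an AE rate nor a capture rate, so both are assumed here. With true rate p and captured share c, the chance of at least one recorded AE among 15 is 1 − (1 − pc)^15.

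- p = 10%: 79% with full capture, 69% with c = 75%, 54% with c = 50%.
- p = 20%: 97%, 91% and 79%.

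This shows how capture could matter. It does not show that capture is poor in this trial.

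**The case against.** The strongest reply is that the clause may condense a fuller definition. The article refers to Korean GCP, an IRB-approved protocol version and SOPs, none of them shown, and the usual seriousness criteria are not printed in it. That would answer a complaint about something left out. Here a definition is stated, in closed form, and other sections rely on it. A loose reading of malfunction might stretch to some of the missing events, but classification would then depend on who reads it.

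Several limits on the concern do stand:

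- **Events do not vanish.** All AEs are documented, recorded and reported to the investigator and IRB. What is lost is the immediacy, the SAE triggers and the SAE count.
- **Leaving the trial does not depend only on the label.** Dropout criteria, item 6, lets the investigator or IRB end participation without it.
- **A reader might infer that AE rates are understated.** The article does not support that. Voluntary reporting carries a risk of under-capture, but staff also record AEs, several listed AEs (bleeding, pallor, fainting) can be seen at the session, and Participant recruitment has the coordinator monitor medical condition, though for adherence. A scripted visit question is the sort of detail an article leaves to the full protocol.
- **A reader might infer that a non-significant test is to serve as proof of safety.** No section says so. Incidence is also to be summarized by group, a small-sample test is named, 95% confidence intervals are mentioned in general terms, and Sample size estimation claims only preliminary evidence.
- **Visit-level changes are largely too late.** Trial status gives the end of recruitment as September 17, 2020, and expected completion by the end of December 2020.

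**Conclusion.** The point holds for the definition. As printed, it excludes a death, a life-threatening event or an admission without severe disability or malfunction from the immediate report, the SAE dropout item, the unblinding exception and the SAE analysis. This rests on a literal reading and on no unseen document overriding the clause. The number of affected events cannot be derived from the article and may be zero.

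The wording on voluntary yet required reporting contradicts itself and may let AEs go uncaptured; that is a risk of unknown size. The limits of 21.8% and 11.6% are a reason to show intervals, not evidence of a wrong analysis. Randomization, the primary endpoint and the efficacy analysis are untouched.

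**What to change.** 1. Widen the SAE definition in Incidence of AEs to the usual seriousness criteria: death, life-threatening event, admission or prolonged stay, persistent or significant disability, or another medically important event.
2. Reconcile the immediate-report rule, Dropout criteria item 2, the exception under Blinding and the SAE analysis with that definition. What the dropout and unblinding rules should be is for the investigators and the IRB to settle.
3. Before analysis, review every recorded AE for seriousness against the widened definition. This remains possible after the visits have ended.
4. Report AE and SAE incidence with exact 95% confidence intervals for each arm and for the two laser arms pooled.
5. Replace the phrase that makes reporting both required and voluntary with a statement of how AEs were in fact ascertained, and note possible under-capture when the results are reported.

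The cost is a wording change with the Ministry and IRB approval that Quality assurance requires for any revision, a review of AEs in at most 45 participants, and one table column. The downside is that the SAE count may rise.
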